### Primary and secondary outcomes

#### Primary outcome

The primary outcome is depressive symptom severity, as measured by the Hamilton Rating Scale for Depression (HRSD_24_) [51], with assessments conducted pre-and post-treatment. The HRSD is likely the most widely used clinician-rated scale for measuring depression. It assesses depressed mood, vegetative and cognitive symptoms of depression, and anxiety symptoms during the prior seven days. Items are rated on either a five-point or a three-point scale, and the total score is derived by summing the individual item scores. Higher scores indicate greater symptom severity. The HRSD has an interrater-reliability of 0.90 [51] and shows high internal consistency (*α* = 0.88) [52]. Furthermore, it is sensitive to change over time and treatment and corresponds well with overall clinical ratings of severity [53,54]. The cut-off points of 10, 19, 27, and 35 represent the thresholds for mild, moderate, severe, and very severe depression, respectively [52].

#### Secondary outcomes

##### Depressive symptomatology

Observer-based ratings of depressive symptom severity will additionally be collected using the 16-item Quick Inventory of Depressive Symptomatology–Clinician-Rating (QIDS-CR_16_) [52] to achieve a more nuanced understanding of the symptom severity. The QIDS-CR_16_ is a brief clinician-report rating scale developed from the 30-item Inventory of Depressive Symptomatology [55,56]. Unlike the HRSD, the QIDS-CR_16_ evaluates only the nine depression criterion symptom domains (i.e., sad mood, concentration, self-criticism, suicidal ideation, interest/involvement, energy/fatigability, sleep disturbance, appetite/weight change, and psychomotor agitation/retardation) from the Diagnostic and Statistical Manual of Mental Disorders (Fifth Edition) [57] during the prior seven days. Each item is scored on a scale from 0 to 3 points, with higher scores indicating higher symptom severity. This measure has shown good psychometric properties, such as strong internal consistency (*α* = 0.85), concurrent validity, and sensitivity to symptom change in patients with MDD [56]. The cut-off points of 6, 11, 16, and 21 represent the thresholds for mild, moderate, severe, and very severe depression, respectively.

Self-reported depressive symptoms will be assessed with the Patient Health Questionnaire (PHQ-9) [58]. This measure has comparable sensitivity and specificity to many other depression measures, although it is significantly shorter than most other measures [59]. The internal reliability of PHQ-9 reaches values between *α* = 0.86 and 0.89. The score ranges from 0 to 27 because each of the nine items can be scored from 0 (“not at all”) to 3 (“nearly every day”). The cut-off points of 5, 10, 15, and 20 represent the thresholds for mild, moderate, moderately severe, and severe depression, respectively [58,59].

##### Quality of life

Health-related quality of life will be measured with the generic EuroQol [60]. The EuroQol includes the EQ-5D and a visual analogue scale. The EQ-5D consists of five items covering five dimensions (mobility, self-care, usual activities, pain/discomfort, and anxiety/depression). The items are rated as causing “no problems”, “some problems”, or “extreme problems”. This questionnaire shows good psychometric properties in terms of validity and reliability in Germany [61].

##### Problem-solving skills

Problem-solving ability (i.e., generalised appraisal, beliefs, expectancies, and emotional responses) will be measured with two subscales of the Social Problem-Solving Inventory-Revised (SPSI-R) [60]. The positive problem orientation (PPO) subscale represents a constructive dimension, whereas the negative problem orientation (NPO) subscale is viewed as a dysfunctional dimension. Both subscales demonstrate strong psychometric properties. Cronbach’s alphas for these subscales are *α* = 0.76 for the PPO dimension and 0.83 for the NPO dimension [62].

##### Behavioural activation

Participants’ activation towards goals/values and pleasant activities as well as avoidance behaviours will be measured with the BADS-Short Form (BADS-SF) [63]. The BADS-SF includes nine items comprising two subscales (activation and avoidance). The items are rated on a seven-point scale. Higher scores indicate that the individual scores high on the area of interest. The BADS-SF shows good psychometric properties. The internal consistency is *α* = 0.82 [63].

##### Worrying

Worrying will be assessed with the ultra-brief version of the Penn State Worry Questionnaire (PSWQ) [64]. This version consists of three items derived from the standard version, with each item being rated on a seven-point scale. The total score ranges from 0-18, with a higher score indicating more worry. The ultra-brief version shows similar psychometric properties as the standard version and an internal consistency of *α* = 0.85 [64].

##### Therapy expectations and helping alliance

Therapy expectations will be assessed with the Patient Questionnaire on Therapy Expectation and Evaluation (PATHEV) [65], which includes the following three scales: hope for improvement, fear of change, and suitability. The items are rated on a three-point-scale. The reliability of the scales has been shown to be good to sufficient (*α* = 0.73-0.89) [65].

Therapeutic alliance will be measured with the Helping Alliance Questionnaire (HAQ) [64]. This self-report questionnaire contains 11 items rated on a six-point-scale and including two subscales: “helpfulness” and “cooperation”. The scale exhibits excellent internal consistency (*α* = 0.89) and test-retest reliability [66,67].

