**Methods:**

In a two-armed randomised controlled trial (*n* = 200), the web-based guided intervention GET.ON-Mood Enhancer-WL in addition to treatment as usual (TAU) will be compared with TAU alone. The intervention contains six modules (psycho education, behavioural activation I & II, problem solving I & II, and preparation for subsequent inpatient depression therapy). The participants will be supported by an e-coach, who will provide written feedback after each module. Inclusion criteria include a diagnosis of MDD assessed with a structured clinical interview [SCID] and a waiting period of at least three weeks before start of inpatient treatment. The primary outcome is observer-rated depressive symptom severity (HRSD_24_). Further (explorative) questions include whether remission will be achieved earlier and by more patients during inpatient therapy because of the web-based preparatory intervention.

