## Methods

### Study design

In this two-armed randomised controlled trial, we will compare GET.ON-Mood Enhancer-WL combined with TAU to TAU alone. The target group will consist of individuals (*n* = 200) who have been referred to inpatient treatment of major depressive disorder by their general practitioner, psychotherapist, or psychiatrist and are awaiting inpatient therapy in one of the German study clinics (Schön Klinik Bad Arolsen/Bad Staffelstein/Bad Bramstedt). The study will be implemented as part of the routine mental health service of the study clinics. Primary and secondary outcome measures will be assessed at baseline, post-treatment (three weeks), at intake for inpatient therapy, weekly during inpatient therapy, and after inpatient therapy. Table 1 gives an overview of the assessments at all planned time points.

**Table 1 T1:** Overview of assessments

**Measure**	**Description**	**Items**	**T**_ **0** _	**T**_ **1** _	**T**_ **2** _	**T**_ **3** _	**T**_ **4** _	**T**_ **5** _	**T**_ **6** _	**T**_ **7** _	**T**_ **8** _	**T**_ **9** _	**T**_ **10** _
			**baseline pre-treatment**	**weekly monitoring**		**post-treatment**	**pre-inpatient therapy**	**weekly monitoring**					**post-inpatient therapy**
SCID	clinical interview, DSM-V criteria		X										
HRSD primary outcome	depressive symptoms, clinician-rated	24	X			X							
QIDS-C	depressive symptoms and severity, clinician-rated	16	X			X							X
PHQ-9	depressive symptoms	9	X	X	X	X	X	X	X	X	X	X	X
Penn State-worry questionnaire–short version	worrying	3	X			X							X
BA-DS–short version	behavioural activation	9	X			X							X
Social problem solving inventory–short version	problem solving	10	X			X							X
EuroQoL	life quality	5	X			X							X
Brief scale for measuring subjective prognosis of gainful employment	subjective prognosis of gainful employment	3	X										
PATHEV	therapy expectations	11	X			X							X
HAQ	help alliance	11	X			X							X

All procedures were approved by the ethics committee at the Philipps University of Marburg in November 2012 (reference number: 2012-37kr). The trial is registered at the German Clinical Trial Register (DRKS00004708).

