#### Treatment as usual (TAU)–control group

TAU includes a wide variety of treatment alternatives, such as antidepressant medication, counselling, face-to-face psychotherapy, or no treatment at all. However, to control for potential confounding effects, treatment utilisation as well as changes in the dose of antidepressant medication will be closely monitored during the study period.

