### Statistical analyses

This clinical trial will be conducted in compliance with the protocol of the Declaration of Helsinki and GCP. Aiming at an intention-to-treat design we will include all participants who will be randomly assigned to conditions. Additional per protocol analyses (PPA) will be conducted, including only participants’ satisfying protocol treatment.

Missing data will be handled using multiple imputations (MI). MI is especially robust with respect to missing data [69]. Nevertheless, to assess systematic effects of missing data that cannot be ignored, pattern mixture analyses for multi-level longitudinal approaches [70] will be conducted. To determine whether the treatment effect is dependent on missing data, the missing-data pattern of each participant will first be coded and then included in a three-way interaction (missing-data pattern x condition x change in depression severity) in the main outcome analyses. If no significant interactions between the missing-data pattern and the treatment outcome are found, it can be concluded that it is very unlikely that missing data skewed the results.

The mean improvement scores on all continuous outcome measures will be analysed within and between groups via mixed-model analyses of variance. For all mixed-model analyses, Cohen’s *d*[71] will be calculated by standardising the differences between baseline and follow-up scores by the pooled standard deviation of baseline scores.

The clinically significant improvements between pre-treatment and post-treatment will be examined with regard to the definition of Kroenke (2002) [58]. Differences in response and remission rates will be analysed using chi-square tests. We will also calculate the number needed to be treated (NNT) to achieve response, partial remission, or remission. Time to remission will be measured in days, and the differences between groups in time to remission will be compared using a t-test for independent samples.

Analyses will be performed using an alpha level of 0.05 and one-sided tests will be used for unidirectional and two-sided tests for bidirectional hypotheses. All analyses will be conducted using SPSS 21.

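### HAQ change from T0, and the T3 between-arm HAQ contrast, are not interpretable as planned, because the person rated differs between visits and arms or may not exist

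*Protocol article*

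**What the plan says.** The section Therapy expectations and helping alliance, under Secondary outcomes, states: "Therapeutic alliance will be measured with the Helping Alliance Questionnaire (HAQ". It describes an 11-item self-report scale with subscales for helpfulness and cooperation. It does not say whom the patient is to rate.

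The Study design section says "Table 1 gives an overview of the assessments at all planned time points". In that table the HAQ row ("help alliance") is marked at T0 (baseline), T3 (post-treatment) and T10 (after inpatient therapy). No arm is excepted.

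The Statistical analyses section then gives one rule for every scale of this kind: "The mean improvement scores on all continuous outcome measures will be analysed within and between groups via mixed-model analyses of variance". The effect size is obtained by "standardising the differences between baseline and follow-up scores by the pooled standard deviation of baseline scores". The HAQ is not exempted from either. Missing data are to be handled by multiple imputation, stated in general terms.

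**The concern.** An alliance score describes a relationship with a particular helper. A change score makes sense only if the same relationship is rated twice, and a contrast between arms only if the two arms rate the same kind of relationship. The schedule and the analysis rule, read together, secure neither. A HAQ improvement from T0 to T3 could record a move from rating nobody, or an outside clinician, to rating an e-coach. A T3 difference between arms could record only that one arm was given someone to rate.

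At stake is how one secondary result is reported. A difference of this kind could be read as an effect on alliance. The informative question, whether preparation on the waiting list alters the later alliance with the inpatient therapist, would stand beside contrasts that do not address it.

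**Working it through.** **The plan's own figure.** The only related number is the sample size, which concerns the primary outcome. With d = 0.40, two-sided alpha 0.05, power 0.80 and equal allocation (assumed), n per arm = 2(1.960 + 0.842)² / 0.40² = 98.1, so 99 per arm and 198 in total. The exact t-test gives 99.08, so 100 per arm and 200 in total, with power 0.804. The stated 200 reproduces, and nothing below depends on it.

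**Who can be rated at each HAQ visit**

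| Visit | Intervention arm | TAU arm |
|---|---|---|
| T0 | No trial helper has acted; possibly an outside clinician | The same |
| T3 | E-coach; possibly also an outside clinician | Possibly an outside clinician; possibly nobody |
| T10 | Inpatient therapist | Inpatient therapist |

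Sources:
- The e-coach's role is in the Methods paragraph of the Abstract: "The participants will be supported by an e-coach, who will provide written feedback after each module". No such feedback precedes T0.
- Inpatient therapy lies at least three weeks ahead for eligible patients (Inclusion and exclusion criteria).
- TAU covers options "such as antidepressant medication, counselling, face-to-face psychotherapy, or no treatment at all".
- Patients are referred "by their general practitioner, psychotherapist, or psychiatrist", so some may already be in care.
- Both arms receive individual inpatient therapy (Inpatient treatment–both groups).

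**What the rule computes.** Write Y(t, h) for the HAQ score at visit t for helper h.

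1. Change to T3 is Y(T3, h3) − Y(T0, h0). In the intervention arm h3 may be the e-coach, who cannot be h0. Without an outside helper, Y(T0, h0) does not exist.
2. Change to T10 is Y(T10, inpatient therapist) − Y(T0, h0). The inpatient therapist cannot be h0 in either arm.
3. The T3 contrast sets a mean that can include e-coach ratings against a mean of outside-clinician ratings from those TAU patients who have such a clinician.
4. Cohen's d divides by the pooled SD of Y(T0, h0), which is defined only for patients with a helper at T0.

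**How many ratings could exist.** Let q be the share of patients with an outside helper. The article does not give q, so the full range is shown, with one q for both visits and 100 patients per arm. T0 ratings = 200 × q; TAU ratings at T3 = 100 × q.

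| q | T0, of 200 | TAU at T3, of 100 |
|---|---|---|
| 0 | 0 | 0 |
| 0.25 | 50 | 25 |
| 0.50 | 100 | 50 |
| 0.75 | 150 | 75 |
| 1 | 200 | 100 |

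At q = 0 the baseline, the change score and d are undefined. Between 0 and 1 they exist for a subset only. At T3 that subset would be set against an intervention arm in which the trial supplies a helper, so the contrast is no longer between the groups as randomised. At q = 1 all scores exist, but in the intervention arm the person rated can still switch between T0 and T3.

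**The case against.** The strongest case on the other side has four parts.

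**The article names no helper, so outside clinicians may be the intended object.** This stands in part. Referral routes and the make-up of TAU make it likely that some patients have someone to rate at T0 and T3. A reader might infer that T0 in both arms and T3 in TAU are unusable for everyone; the documents do not show that. But an outside clinician at T0 does not give a common object of rating once the e-coach or the inpatient therapist is rated later.

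**Item wording, the helper named at each visit and a not-applicable option belong in a fuller document.** Their absence alone would indeed be no finding. The point rests on two things that are stated: the visit schedule and the rule for all continuous outcomes. A later plan could repair the result only by departing from that rule or by fixing one referent throughout, and the second would leave out the e-coach and the inpatient therapist.

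**Randomisation protects the T10 contrast.** Subtracting a heterogeneous T0 score would mainly cost precision there, provided T0 scores exist and allocation does not affect them. This largely stands. The proviso is not settled, because the section on eligibility and randomisation mentions allocation before the initial assessment, and participants are not blinded. Nor does the argument rescue within-group change or the T3 contrast.

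**Multiple imputation is stated only in general.** This stands. A reader might infer that the plan will impute alliance where there was no helper. The text does not say so; it only fails to rule it out.

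It is also true that no HAQ hypothesis appears in the trial objectives or the Discussion, so no main conclusion rests on this scale.

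**Conclusion.** The concern holds in a limited form. As planned, HAQ change from T0 and the HAQ contrast between arms at T3 cannot be interpreted, because the person rated may differ between visits and arms or may not exist.

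It would be tempting to go further and say that the HAQ result has no meaning. The documents do not support that. At T10 both arms can rate an inpatient therapist, so a comparison of T10 scores is interpretable. At T3 the intervention arm's scores can describe the alliance with the e-coach.

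The conclusion assumes that Table 1 applies to both arms, as its lack of any restriction implies, and that the e-coach is a person whom intervention patients would rate at T3. It does not depend on the share with an outside helper, which sets only how many T0 and TAU T3 ratings exist. One secondary measure is affected; the primary outcome and the sample size of 200 are not. The point is minor, but cheap to correct.

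**What to change.** - Exempt the HAQ from the improvement-score rule and from the baseline-standardised d.
- Name the person to be rated at each visit.
- Compare arms on the T10 HAQ score for the inpatient therapist, with no change from T0.
- Report T3 HAQ in the intervention arm descriptively, as alliance with the e-coach.
- Drop HAQ at T0 and, in TAU, at T3. Alternatively, keep these ratings only for patients with a named outside helper and report them descriptively.
- State that the HAQ is not imputed where there is no helper to rate.

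The cost is one row of Table 1 and one or two sentences of analysis text. Dropping the ratings reduces questionnaire burden but loses some descriptive data on alliance in outside care; the restricted alternative keeps them. Pre-treatment expectations remain covered, since the PATHEV is also scheduled at T0.

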##### Response remission, and time to remission

Based on the recommendation of Rush (2006), we will use a definition of response/remission that reflects a clinically significant benefit, depending on the specific setting and needs in this trial [68]. A decline in the PHQ-9-score of at least five points will be taken as a clinically significant response. Remission in this specific context will be understood as a symptom-free state, an absolute PHQ-9-score of less than ten will be defined as partial remission, and a PHQ-9-score of less than five will be defined as remission [58]. Time to remission will be defined as the number of days until the symptom-free state is achieved for the first time.

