### Blinding

The research staff conducting the observer-based rating of depressive symptoms will be blinded to the participants’ assigned conditions. Considerable effort is being undertaken to ensure blindness, including the following: (a) an explanation to the participants as to why it is important not to inform the interviewer about the condition to which they were assigned, (b) a written reminder in the interview manual prompting the interviewer to ask the participant not to inform him or her about the randomisation status, (c) verbal reminders to the patient before the interview, and (d) a documentation after the assessment of whether or not the interviewer is still blind to the treatment condition. If the interviewer finds out about the treatment condition another independent interviewer will conduct the interview instead. Participants will not be blinded to the treatment condition.

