### Sample size

This study will be designed to detect a difference of *d* = 0.40 between the groups as the primary outcome. As patients expect to be treated for their depression in the subsequent inpatient psychotherapeutic treatment, we do expect a somewhat smaller effect size for our intervention than what has been found in the most recent meta-analysis of internet-based guided self-help treatments for depression [35]. With a power of 0.80 in a two-tailed test and *α* = .05, a sample of *n* = 200 participants would need to be included at baseline (calculated using GPower 3.1).

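### Response, remission and NNT rest only on unblinded self-report (PHQ-9); the blinded QIDS-C already collected at T3 and T10 should be co-reported as a remission rate

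*Protocol article*

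**What the plan says.** Under the heading on response, remission and time to remission, the Protocol article fixes all three binary outcomes on one instrument. For response: "A decline in the PHQ-9-score of at least five points will be taken as a clinically significant response". Partial remission is a PHQ-9 score under ten, and for full remission "a PHQ-9-score of less than five will be defined as remission". Statistical analyses compares response and remission rates by chi-square test and derives an NNT for response, partial remission and remission.

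The secondary-outcome section describes the PHQ-9 as self-reported. Blinding says "Participants will not be blinded to the treatment condition", while the staff who make the observer ratings of depression are blinded. The limitations part of the Discussion acknowledges that there is no attention control.

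Table 1 (Study design) lists the QIDS-C as "depressive symptoms and severity, clinician-rated" and schedules it at T0 (baseline), T3 (post-treatment) and T10 (after inpatient therapy). The HRSD, the primary outcome, is scheduled at T0 and T3 only. For the QIDS-C, the section on depressive symptomatology states: "The cut-off points of 6, 11, 16, and 21 represent the thresholds for mild, moderate, severe, and very severe depression, respectively". No response or remission rule uses these thresholds.

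**The concern.** The Discussion sets out to ask whether more patients are in remission or response at the end of inpatient treatment. The answer will come from a questionnaire completed by people who know whether they received the online programme. The inclusion criteria require them to be motivated to take part in it, and the comparator may be no treatment at all. In such a design, self-report is open to expectation effects in either arm.

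A rating by a blinded interviewer exists at the same two key times, with a threshold that the protocol itself prints, yet no binary outcome uses it. The Discussion lists blinded clinician ratings, alongside self-report, as a strength of the trial. That strength does not reach the remission rates or the NNTs. An NNT is easily quoted outside its context, and the Abstract links higher remission rates to shorter inpatient therapy and lower costs. A blinded definition added after unblinding would look post hoc, so it should be fixed in advance.

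**Working it through.** **1. The plan's own figure.** The only related figure is the sample size for the primary outcome: d = 0.40, "With a power of 0.80 in a two-tailed test", alpha 0.05, 200 in total. The normal approximation gives 2 × (1.960 + 0.842)² / 0.40² = 98.1, so 99 per arm and 198 in total. The exact noncentral-t calculation gives 100 per arm, 200 in total, with power 0.804. The figure reproduces and is not in question. It supplies the 100 per arm used below, with 1:1 allocation and no dropout assumed.

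**2. Which depression measure is blinded, and how it is used.**

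| Measure | Rater | Times (Table 1) | Planned use |
|---|---|---|---|
| HRSD | blinded clinician | T0, T3 | primary, continuous |
| QIDS-C | blinded clinician | T0, T3, T10 | continuous only |
| PHQ-9 | unblinded patient | T0 to T10 | continuous; all response, remission, NNT and time to remission |

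At T10 the QIDS-C is the only blinded depression rating. Between T3 and T10 only the PHQ-9 is measured, so time to remission cannot be moved to a blinded instrument.

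**3. Size of a possible reporting shift (illustration).** The documents give no PHQ-9 mean or SD near discharge, no expected remission rate and no size of bias. All of these are assumptions. With normal scores and a half-point continuity correction, P(PHQ-9 < 5) = Φ((4.5 − mean)/SD). A 1-point downward shift in one arm, with no true effect, changes this to Φ((5.5 − mean)/SD).

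- Mean 8, SD 5: Φ(−0.70) = 0.242 becomes Φ(−0.50) = 0.309, a change of 6.7 percentage points.
- Mean 6, SD 4: 0.354 becomes 0.450, a change of 9.6 points. This is the largest over means 6, 8, 10 and SDs 4, 5, 6.
- Mean 10, SD 4: 0.085 becomes 0.130, a change of 4.6 points. This is the smallest.

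The corresponding spurious NNTs run from 1/0.096, about 10, to 1/0.046, about 22.

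**4. Would such a shift reach significance?** With control rate p0 and shift b, p1 = Φ(Φ⁻¹(p0) + b/SD). The chance of a significant result in that direction is Φ((p1 − p0 − z·se0)/se1), where se0 is the pooled and se1 the unpooled standard error with 100 per arm. For p0 = 0.30, SD 5, b = 1: p1 = Φ(−0.524 + 0.200) = 0.373, and the chance is about 0.19 (two-sided 0.05).

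Over p0 of 20% to 40% and SD of 5 to 6:

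| Shift (PHQ-9 points) | False difference (percentage points) | Chance, two-sided 0.05 |
|---|---|---|
| 0.5 | 2 to 4 | 6% to 8% |
| 1 | 5 to 8 | 13% to 20% |
| 2 | 11 to 16 | 40% to 61% |

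Statistical analyses also allows one-sided tests for directional hypotheses; the 1-point case then gives 21% to 30%. In the most extreme case of step 3 (mean 6, SD 4) the two-sided chance is Φ((0.0964 − 1.96 × 0.0693)/0.0690) = Φ(−0.57), about 28%. A 1-point shift would therefore usually stay non-significant.

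**The case against.** The strongest reply is that nothing here is an error or a contradiction. The PHQ-9 thresholds are explicit and cited, and the PHQ-9 is the only depression measure taken at every time point, so one instrument serves response, remission rates and time to remission. That is a sound reason to keep it, and an argument against making the QIDS-C the lead definition, which would put remission rates and time to remission on different scales.

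Four further points stand:

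- Remission during inpatient therapy is labelled exploratory in the Abstract and in the trial objectives. The main hypothesis rests on the blinded HRSD.
- Statistical analyses covers all continuous outcomes by mixed models, so the QIDS-C at T10 already gives a partial blinded check. It does not give a remission rate or an NNT.
- The QIDS-C is rated by telephone interview with an unblinded patient, and several domains depend on what the patient says. Rater blinding reduces expectation effects but does not remove them.
- By T10 both arms have had inpatient therapy, usually 21 to 56 days, so an effect of knowing the earlier allocation may have weakened.

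A reader might infer that the remission result is biased, or that reporting bias alone would make it significant. The documents show an exposure to bias, not its presence, and the calculation rests on assumed shifts. A reader might also infer that the Discussion claims blinded remission rates. It claims blinded ratings in addition to self-report, which is accurate.

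What remains is that the rates and NNTs have no blinded counterpart, although the data for one will be collected.

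**Conclusion.** The point holds as a low-cost improvement to an exploratory analysis. It does not touch the primary inference or the sample size. As planned, a difference in response or remission rates, with its NNT, can be supported only as a self-report finding. If PHQ-9 scores near discharge have a mean of 6 to 10 and an SD of 4 to 6, a 1-point reporting shift in one arm changes the remission rate by about 5 to 10 percentage points. With 100 per arm it reaches two-sided significance in roughly 13% to 20% of trials at SD 5 to 6, and about 28% in the most extreme case examined. Only a shift of about 2 points would make a false positive result likely (40% to 61%). The actual size and direction of any shift are unknown. The documents do not support the stronger reading that the bias is wholly avoidable: time to remission must stay on the PHQ-9, and a blinded interview still carries the patient's own expectations.

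**What to change.** Prespecify, beside the PHQ-9 rates, a remission rate defined as QIDS-C below 6 at T3 and at T10. Report for each the difference between arms, its confidence interval and the NNT. State that 6 is the protocol's threshold for mild depression, used here as a remission cut-off in the same way as the PHQ-9 cut-off of 5.

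Keep the PHQ-9 definitions, and keep the PHQ-9 for time to remission. Add a sentence on interpretation: a remission-rate benefit is described as supported only if the QIDS-C difference points the same way; otherwise it is reported as a self-report finding only. Agreement in direction is enough as a rule, since the documents offer no basis for a criterion on size. Note in the limitations that rater blinding reduces but does not remove patient expectation effects.

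Cost: no new visit, instrument or patient, and one more table. The downside is that two definitions are reported and they may disagree.
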